Research suggests that the post-natal environment may buffer the effects of prenatal maternal mood on child outcomes. [name]’s group found that maternal sensitivity moderated the impact of maternal antenatal anxiety on the child’s cognitive and behavioral outcomes at 7 months [45, 71]. There are no data, however, on whether maternal sensitivity can moderate the effects of an independent prenatal maternal stressor on child outcomes. By the same token, it is unknown whether an objective, independent stressor in humans will influence maternal behaviors, like sensitivity, which may then mediate effects of PNMS on the child. Thus, we hypothesize that objective exposure and subjective stress from the floods will predict HPA stress reactivity and cognitive development in QF2011 infants, and that this association may be mediated and/or moderated by maternal sensitivity.(5)How do pre-existing levels of depression interact with peritraumatic responses to the Queensland floods to influence the trajectory of maternal mental health following exposure?

Because a measure of perinatal depression (the Edinburgh Postnatal Depression Scale (EPDS)) is administered routinely to all women in Australia at the time of hospital booking, levels of pre-existing maternal depression are available for our subgroup of QF2011 women who had already booked at the Mater hospital prior to the floods. Therefore, the QF2011 study is in a position to respond to unanswered questions about the natural history of maternal mental health in response to a disaster. We predict that depression before exposure to the disaster will interact with levels of distress and dissociation at the time of the flooding (i.e., ‘peritraumatic’) to explain variance in postpartum levels of depression, anxiety, PTSD-like symptoms, and positive mental health.(6)If variance in physical characteristics, like fingerprint asymmetry and finger length ratios, are explained by levels of objective and subjective PNMS, what biological processes are they markers for?

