[name] and [name] have found that PNMS from the Québec ice storm explains significant variance in physical markers associated with neurodevelopmental disorders, such as dermatoglyphic (fingerprint) asymmetry [54], and the ratio of the lengths of the second and fourth fingers (2D:4D ratio) which is reputed to reflect *in utero* exposure to testosterone [72, 73]. But it is unknown by what process PNMS influences 2D:4D ratios and dermatoglyphic asymmetries. Once it is determined which biological variables in placenta and cord blood are sensitive to PNMS, we will determine which of these, if any, are then correlated with these neurodevelopmental markers in hands.(7)To what extent do the severity of prenatal maternal objective/subjective stress, and/or maternal cortisol during pregnancy pre-flood, predict the HPA axis function of the infant/child, and what other outcomes are associated with altered HPA axis function?

Prenatal maternal stress research, particularly in animal models, has demonstrated the effects of PNMS on the development of the fetal HPA axis, which regulates the stress response (Glover et al., [74]; Charil et al., [5]). In humans, fetal exposure during early to mid-pregnancy, the period during which the HPA axis develops, seems particularly deleterious [75, 76]. Alterations in HPA axis have also been shown to be associated with a wide range of neurodevelopmental, psychiatric and metabolic outcomes [74, 77]. We aim to determine whether it is mere objective exposure to the stressor, or the maternal subjective distress, that accounts for altered HPA axis function in the infant/child, and which outcomes (e.g., attention, emotional difficulties, learning and memory recall, obesity) are associated with altered function.

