#### Data analysis and power

Our analyses of the QF2011 data will proceed in a highly structured manner, according to our underlying explanatory model. This model posits that objective stress and cognitive appraisal predict peritraumatic stress responses, which predict both subjective stress reaction (PTSD symptoms) and maternal HPA axis response. We hypothesize that at least some of these aspects of maternal stress may influence maternal mental health and may also influence variables within the placenta and fetus (cord blood); thereby influencing fetal/child physical/physiological development (growth & body composition, fingerprints or finger length ratios, HPA axis) and child neurodevelopment (cognitive, behavioral, and motor development). We further suggest that at each level of the cascade there may be genetic moderation and epigenetic mediation; and also moderation of outcomes by pre-disaster maternal characteristics (e.g., depression, socioeconomic status), and by the sex of the infant. Finally, our results may indicate a moderating effect from prenatal care (MGP versus standard care) and maternal caretaking behaviors. Below, we present a sampling of statistical approaches we will take to the data analysis.

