##### Maternal mental health

Next, we will examine genetic and psychosocial mediators and moderators of the associations between flood stress and 12-month post-flood maternal outcomes such as symptoms of anxiety (STAI) and PTSD, as well as positive mental health (MHC-SF). We will test the ability of maternal coping style (Brief COPE) and specific candidate genes to moderate the effects of objective stress exposure on mental health outcomes. For women who had the EPDS administered before the floods, we will also determine the moderating effects of pre-flood depression (as measured by the EPDS) in the association between objective stress exposure and maternal mental health outcomes. Our general approach is to use hierarchical multiple linear regression, adding variables into the equation one block at a time. We first regress maternal mental health on exogenous variables such as maternal genotype and demographics; next, we add objective stress exposure; peritraumatic distress and dissociation; then psychosocial variables needed for the interaction (e.g., coping style); and finally we test one interaction at a time (e.g., objective stress-by-coping). We also test moderation and mediation effects directly using the SPSS PROCESS command; the mediation analyses include bootstrapping.

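### Research question 6 asks by what process prenatal stress affects hand markers, but its only stated step is a correlation that shared dependence on stress can produce without any such process

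*Protocol article*

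**What the plan says.** Question 6, in the section on problem statement, objectives, hypotheses and research questions, is conditional. It opens "If variance in physical characteristics, like fingerprint asymmetry and finger length ratios, are explained by levels of objective and subjective PNMS" and then asks "what biological processes are they markers for". The paragraph beneath gives the gap in mechanistic terms: "it is unknown by what process PNMS influences 2D:4D ratios and dermatoglyphic asymmetries". Two steps follow. The first finds the placental and cord-blood variables that respond to stress ("Once it is determined which biological variables in placenta and cord blood are sensitive to PNMS"). The second is: "we will determine which of these, if any, are then correlated with these neurodevelopmental markers in hands".

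Other sections bear on this link without fixing a test for it:

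- **Data analysis and power** puts the hand markers downstream of placenta and cord blood in the general explanatory model, in the list "growth & body composition, fingerprints or finger length ratios, HPA axis".
- **Maternal mental health** plans direct tests of moderation and mediation, and says that "the mediation analyses include bootstrapping".
- **Birth biologicals** starts from bivariate associations and ends in structural equation modelling. It names two cascades, one through cortisol to the child's HPA axis and one through the catecholamine and inflammatory system.
- **Child development** applies regression models like the maternal ones to the effects of stress on child outcomes, including physical development. It names neither hand markers nor birth biomarkers.

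**The concern.** A question about the process by which stress changes a hand marker is a mediation question. It needs the biomarker-to-marker path after the part of both variables that stress explains has been taken out. A marginal correlation does not do this.

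Here the omission matters because of how the question is built. The first step keeps biomarkers because they depend on stress, and the premise requires that the hand markers depend on stress too. A correlation between them is therefore expected even if neither influences the other. Nor do the two steps together form a joint-significance test of mediation, because that test also needs stress in the model for the second path.

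At stake is the reading of the answer. A placental or cord-blood variable with no role in hand development could pass both steps and be taken as evidence about mechanism. The rates below are per biomarker, and the three maternal-placental-fetal models list many.

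**Working it through.** The document states no sample size, alpha, power or effect size for question 6, so there is no figure to reproduce.

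**Inputs**

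- n = 175: families giving data at 2½ years (Power). This is illustrative, because the number with both birth samples and hand measures is not stated.
- n = 167: families projected for the 4-year assessment (Power; 0.80 × 209 = 167.2).
- n = 100: assumed, to allow for incomplete birth samples.
- Two-sided alpha 0.05: assumed.
- Standardised effect of stress on the biomarker (a) and on the hand marker (b): assumed, a = b = 0.2, 0.3, 0.4.

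**Step 1: induced correlation.** Suppose stress S affects biomarker B and hand marker H, with no path from B to H. Then corr(B, H) = a × b, which is 0.04, 0.09 and 0.16 for the three settings. The partial correlation given S has numerator corr(B, H) − a × b = 0.

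**Step 2: chance that the induced correlation is significant.** By Fisher z, with f = atanh(ab) × √(n − 3), the chance is Φ(f − 1.96) + Φ(−f − 1.96).

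For a = b = 0.3 and n = 175: f = 0.0902 × √172 = 0.0902 × 13.11 = 1.18. The chance is Φ(−0.78) + Φ(−3.14) = 0.219 + 0.001 = 0.22.

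| a = b | Induced r | n = 175 | n = 167 | n = 100 |
|---|---|---|---|---|
| 0.2 | 0.04 | 8.2% | 8.1% | 6.8% |
| 0.3 | 0.09 | 22.0% | 21.2% | 14.4% |
| 0.4 | 0.16 | 56.2% | 54.3% | 35.6% |

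**Step 3: effect of selection and of adjustment.** Simulation with 20,000 replicates per setting. The selected columns keep only replicates in which B and H were both significantly related to S.

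| n | a = b | Plain correlation, all | Plain correlation, selected | Partial correlation given S, selected |
|---|---|---|---|---|
| 167 | 0.2 | 8.2% | 10.2% | 5.5% |
| 167 | 0.3 | 20.8% | 21.5% | 5.2% |
| 167 | 0.4 | 54.4% | 54.5% | 4.8% |
| 100 | 0.2 | 7.0% | 10.6% | 5.1% |
| 100 | 0.3 | 14.6% | 17.3% | 5.0% |
| 100 | 0.4 | 35.3% | 36.0% | 5.0% |

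At n = 175, keeping biomarkers significantly related to S gives 9%, 22% and 56%, almost the same as the unselected Fisher figures.

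The inflation thus comes from the common cause. Selection adds at most about 4 percentage points (n = 100, weakest effects) and almost nothing at 0.4. Conditioning on a perfectly measured S brings the rate back to about 5%.

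**The case against.** The strongest reply is that the sentence belongs to the research-question narrative of a condensed article, whose analysis section says it presents only a sample of approaches. Saying that variables are correlated does not commit the authors to an unadjusted test. Mediation with bootstrapping and structural equation modelling are both in the plan, and the explanatory model places hand markers downstream of placenta and cord blood. A marker relation is also associational, and the text promises only to see which variables, if any, correlate.

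Much of this stands. A reader might infer that the study plans no mediation analysis that could serve here. The document does not support that, because the tools are named. A reader might also infer that correlated biomarkers will be declared the mechanism. The text does not say so; that would be a prediction about reporting.

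What does not stand is that the link is already covered. Bootstrapped mediation is described for maternal outcomes, the structural equation models are tied to two cascades that do not include hand markers, and the child-development models do not name birth biomarkers. The only step stated for the biomarker-to-hand-marker link is correlation, offered in answer to a question about process. That is a stated step unsuited to its question, not a detail left to a fuller plan.

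**Conclusion.** The point holds as a matter of logic: the stated step cannot separate a biological process from shared dependence on stress. Its size is conditional. The per-biomarker false-positive rate at n = 175 is about 8-9%, 22% and 56% for assumed stress effects of 0.2, 0.3 and 0.4 on both variables, against about 5% with stress in the model. At 0.2 the inflation is modest; it becomes severe only near 0.4, and the document does not say where the true effects lie. With fewer complete pairs of birth sample and hand measure the rates fall, as the n = 100 figures show.

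Two stronger readings should be avoided. One is that choosing stress-sensitive biomarkers drives the error; the simulation shows that selection contributes little. The other is that adjustment restores the 5% rate in practice. That result assumes one perfectly measured stress variable. The IES-R asks about current symptoms, was sometimes completed after birth, and its recruitment scores were regression-imputed for about 50 women. Adjustment therefore removes only the measured part of the shared cause, and other shared causes could remain.

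This is one secondary question and does not affect the study's primary question.

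**What to change.** Under question 6, state that each association between a biomarker and a hand marker will be tested with objective and subjective stress (QFOSS and IES-R) in the model, or as a bootstrapped indirect effect using the mediation or structural equation tools already named under Maternal mental health and Birth biologicals. Describe any unadjusted correlations as descriptive only. When reporting, note that residual confounding by imperfectly measured stress may remain.

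The cost is about one sentence of analysis wording, with no new data or procedures. The downside is small: slightly wider intervals for the adjusted associations.

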## Methods/design: QF2011

### Participants

All women who agreed to participate in the study provided written informed consent. Inclusion and exclusion criteria differed slightly for M@NGO [63, 64] and for QF2011. Women were eligible for recruitment to the M@NGO trial if they were less than 24 weeks pregnant and were not planning caesarean section birth; QF2011 participants had to have been pregnant with a singleton pregnancy (at any gestation) and residing in the general vicinity of Brisbane on January 10, 2011. All participants were 18 years of age or older at recruitment, and were able to speak English fluently.

Recruitment for QF2011 began as soon as ethics approval was received (April 4, 2011), and continued to mid-January 2012 (12 months after the peak of the flood); as per original protocol, recruitment for M@NGO ceased on May 31, 2011 in both Sydney and Brisbane. Recruitment proceeded in 4 ways:When new participants were recruited into M@NGO, they were also presented with the QF2011 protocol, and invited to participate in either or both studies. M@NGO recruitment at the Mater Hospital involved face-to-face, phone, and e-mail recruiting following a routine mail-out describing the study to all women attending the antenatal clinic.The team contacted all existing M@NGO subjects who were eligible for QF2011 first by e-mail, then by cell phone (text message), then by telephone inviting them to also participate in the new flood study.The team invited women who were pregnant and eligible for the QF2011 study, but not eligible for M@NGO, or who would have been eligible for M@NGO but were approached after M@NGO recruitment ceased, to participate in QF2011. A flyer inviting women to participate and to contact the recruitment team was included in the routine mail-out from the antenatal clinic. A researcher in the antenatal clinic actively recruited participants face-to-face on site and was available to speak to midwives and other potential participants about the study.Finally, advertisements were placed in local newspapers, on radio, and on the internet for women who were pregnant at the time of the floods (even if they had already delivered).

As such, this study included 2 main groups of participants:QF2011 women enrolled in M@NGO (n = 108, including 1 intrauterine death). These participants were enrolled in both M@NGO and QF2011. Some were already M@NGO study participants at the time of the floods and where subsequently recruited to QF2011; others were pregnant at the time of the floods and were recruited into both studies simultaneously. At recruitment to the QF2011 study, M@NGO women may still have been pregnant or they may have already given birth as the inclusion criteria stated only that they must have been pregnant on January 10, 2011.QF2011 women not enrolled in M@NGO (n = 122). This group included women who had declined participation, did not meet the selection criteria for the M@NGO study, or who were recruited after the close of M@NGO (May 31, 2011).

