We also hypothesize that the effects observed in models 1-3 in placental function and in children will be more important for male fetuses compared to female fetuses.(2)Midwifery Group Practice (MGP) care (in comparison with standard care) will protect pregnant women and their unborn children from the impact of objective levels of exposure and subjective levels of maternal distress arising from the 2011 Queensland floods.

Project Ice Storm found multiple effects of objective stress exposure on child outcomes*.* Although psychosocial treatments may reduce maternal anxiety and subjective stress after a disaster [69], they cannot alter the objective hardship and danger that was faced. Because QF2011 is piggy-backed onto the M@NGO study, we have a built-in RCT of prenatal care that commenced before the flooding that may demonstrate protective properties of this more personalized, and supportive, coordinated midwifery approach. We hypothesize that MGP care will buffer effects of flood stress (objective and/or subjective) on maternal outcomes, such as PTSD symptoms and depression, on perinatal outcomes (e.g., gestation length and birth weight), and on child outcomes.(3)Maternal and child genotypes will moderate the effects of PNMS on outcomes. Some examples of such gene-by-environment interactions are listed here:Maternal mental health:i.We hypothesize that maternal PTSD symptom severity (1 year post flood) may be explained by interactions between objective stress (especially Threat) and the maternal 5-HTTLPR (serotonin-transporter-linked polymorphic region) of the *SLC6A4* gene, controlling for potential confounders.ii.Postpartum (and continuing) maternal depression may involve interactions between objective stress (especially Loss) and the maternal 5HT2A gene (serotonin receptor 2A), controlling for potential confounders.Child stress reactivity:i.The effects of PNMS on the child’s HPA axis will be moderated by infant genotypes associated with the stress response, such as CRH, CRHR1.Epigenetics: Since Project Ice Storm has shown that maternal objective stress predicts DNA methylation in children at age 13 years [70], QF2011 will also endeavor to obtain biological samples throughout childhood for testing epigenetic hypotheses at a later date.(4)Does maternal sensitivity mediate, or moderate, (or both) the effects of PNMS on child outcomes?

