##### Child development

We will again use hierarchical linear multiple regression to test the effects of PNMS on child physical, cognitive, behavioral and motor development at each age, testing models similar to those described above for maternal mental health. For those variables that will be assessed at multiple time points (e.g., Ages and Stages, and CBCL), we will employ multi-level modelling once all of the data are obtained at age 4 years. This approach will determine the effects of PNMS on the initial measures of child functioning, and then on the slope of change in functioning over time.

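### Preterm birth cannot be observed after late-pregnancy flood exposure in women enrolled before birth, so flood-timing effects on gestation length and preterm birth are left-truncated in the birth-biological models and open to bias of either sign in the pooled cohort

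*Protocol article*

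**What the plan says.** Under Participants, a woman was eligible if she was "pregnant with a singleton pregnancy (at any gestation") and "residing in the general vicinity of Brisbane on January 10, 2011". On dates, the same section says: "Recruitment for QF2011 began as soon as ethics approval was received (April 4, 2011), and continued to mid-January 2012".

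There were four routes in. Two take women who are still pregnant: joint enrolment with M@NGO, and the antenatal-clinic approach. Two do not require it. Of the existing trial participants it says "The team contacted all existing M@NGO subjects who were eligible for QF2011 first by e-mail", and later that "M@NGO women may still have been pregnant or they may have already given birth". The advertisements sought women "on the internet for women who were pregnant at the time of the floods (even if they had already delivered"). Participants are then grouped by M@NGO membership (108 in, 122 out), not by whether consent came before or after birth. The section on enduring distress adds that about 50 women joined more than 10 months after the flood.

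Birth outcomes are study targets. Hypothesis 2 expects midwifery care to buffer flood effects "on perinatal outcomes (e.g., gestation length and birth weight), and on child outcomes". Model 2 names preterm birth as a consequence of placental inflammation. The Birth biologicals part of the analysis section plans to test moderation by the gestational timing of the flood. The overall aim is to replicate and extend Project Ice Storm, whose reported findings include shorter gestation after second-trimester exposure.

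**The concern.** When consent can fall before or after birth, who is observed may depend on the outcome being studied. Two mechanisms need to be kept apart.

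- **Left truncation.** A woman who enrols while pregnant has not delivered before her gestation at consent. Because consent could not start until 12 weeks after the flood, the preterm births she could still show depend on how far along she was when flooded. Gestation at exposure is the moderator that the study wants to test, so a timing effect can arise from the recruitment calendar alone.
- **Self-selection after birth.** A woman who joins after delivery knows both how badly she was flooded and how the birth went. If joining depends on the two together, a severity effect can be distorted.

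The quasi-random distribution of flood harm, on which the article relies, protects against neither, because both act through entry to the study.

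**Working it through.** The article states no sample size, effect size or preterm rate for these outcomes, so there is no figure of its own to reproduce.

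**Date arithmetic (inputs from the article)**

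1. 10 January to 4 April 2011 = 84 days; 84 / 7 = 12.0 weeks.
2. Term begins at 37 weeks; 37 - 12 = 25. A woman at 25 weeks or more at the flood and undelivered on 4 April was at 37 weeks or more. Her preterm birth, had there been one, could enter only through post-birth enrolment.
3. The latest possible 42-week date for a woman pregnant on 10 January is 10 January + 294 days = 31 October 2011. Ten months after the flood is 10 November. All of the approximately 50 late recruits had therefore delivered: 50 / (108 + 122) = 50 / 230 = 22%. This is a floor, since others may also have consented after birth.
4. Table 1 marks placenta, umbilical cord and cord blood as QF2011 samples. The Placenta and Cord blood sections describe collection at delivery, and the 36-week blood came from women still pregnant at recruitment. Essentially all contributors were thus enrolled before birth, and step 2 applies to them in full.

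**Simulation (assumptions not in the article)**

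Gestation at flood was uniform over 4-42 weeks, keeping women undelivered at the flood. The preterm rate was 8%, with preterm gestation equal to 37 weeks minus a gamma variable (shape 1.5, scale 1.6 weeks). Term births were normal (mean 39.5, SD 1.2), clipped to 37-42.5. There was no true flood effect. In the pooled columns, women are classed by delivery before 4 April. Entries are preterm rates (%).

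| Flooded at (weeks) | All pregnant at flood | Antenatal set, consent at 12 weeks | Antenatal set, consent spread over 12-20 weeks | Pooled, equal joining | Pooled, delivered women join at 0.3 times the rate | Same, preterm mothers at twice the rate of other delivered women |
|---|---|---|---|---|---|---|
| 4-14 | 8.0 | 8.0 | 7.9 | 8.0 | 8.1 | 8.1 |
| 14-25 | 8.1 | 6.4 | 4.3 | 8.1 | 6.9 | 7.4 |
| 25-37 | 6.5 | 0.0 | 0.0 | 6.5 | 4.4 | 8.5 |

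The 6.5% in the first data column is below 8% only because a woman must still be pregnant to be flooded late. It is not a recruitment effect.

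With assumed preterm rates of 6% and 10% and consent at 12 weeks, the antenatal set shows 4.8% and 8.0% for exposure at 14-25 weeks (true 6.0% and 10.0%), and again zero for 25-37 weeks.

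For gestation length in the pooled cohort, the null difference between exposure at 25-37 and 4-14 weeks is 39.21 - 39.11 = 0.10 week. With delivered women joining at 0.3 times the rate it becomes 39.48 - 39.11 = 0.37 week.

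**Flood severity, no true effect, delivered women joining at 0.3 times the rate**

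- No joint dependence of joining on severity and outcome: difference in preterm risk about 0.
- Highly exposed preterm mothers join at 2 times the rate: +1.0 point, -0.05 week.
- At 3 times: +2.0 points, -0.10 week.
- At 0.5 times: -0.5 point.
- With a true 0.5-week shortening and delivered women joining at 0.1-0.3 times the rate, without joint selection, the estimate is -0.49 to -0.50 week.

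**The case against.** The strongest reply is that the study as a whole is not truncated at 12 weeks. A reader might infer that every participant had to stay pregnant until April 2011, but the only gestational condition is pregnancy on 10 January. Women who delivered in between could join later, and existing M@NGO participants were all contacted from a list formed before birth. With equal joining the pooled bias is nil, as the table shows. This stands, and it limits the firm conclusion to the antenatally enrolled set. It does not clear the pooled cohort: the article gives no reason to expect clinic-approached pregnant women and self-referring mothers to join at the same rate.

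A reader might also infer that flood-severity estimates are biased. The documents do not support that. It needs joining to depend jointly on exposure and outcome, no figure bears on this, and the sign could go either way. For the M@NGO women (108 of 230) invitation could not depend on the outcome, although consent could.

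It is also fair to say that the article offers only a sample of its analyses, and that delayed entry and sensitivity sets often sit in an analysis plan. The Child development regressions ("We will again use hierarchical linear multiple regression to test the effects of PNMS on child physical, cognitive, behavioral and motor development at each age") concern later ages and are not evidence of how birth outcomes will be modelled. But the recruitment rule and the timing-moderation test are fixed here, and together they create the problem.

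Finally, self-selection after birth hardly touches the placental and cord-blood models, because late joiners cannot supply those samples. That is correct, and it is why truncation there is complete and not offset.

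**Conclusion.** The point holds in two parts of different strength.

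- **Firm, by date arithmetic alone:** among women enrolled while pregnant, including essentially all who gave 36-week blood, placenta and cord blood, flood exposure at 25 weeks or later can show no preterm birth. Exposure somewhat earlier shows too few: 6.4% or 4.3% against about 8% for 14-25 weeks under the assumptions above. The timing-moderation test in the birth-biological models is left-truncated for gestation length and preterm birth.
- **Conditional:** in the pooled cohort the same contrast is open to bias in either direction, from 6.5% to 4.4% or 8.5% for late exposure in the scenarios run. The size rests on assumed joining rates, and the article does not report the split by birth status at consent.

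Bias in severity effects is a possibility only. It was at most 2 points or 0.1 week in the scenarios examined. Nothing here bears on maternal mental-health outcomes, and the argument about truncation does not extend to later child outcomes as such.

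**What to change.** This is a change of analysis only, using consent and birth dates that should already be held.

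1. Tabulate women by consent before or after birth, and by gestation at consent for those still pregnant, across flood-timing windows.
2. For gestation length and preterm birth, use a time-to-birth model with delayed entry at gestation at consent for women enrolled while pregnant.
3. Limit preterm-by-timing claims, above all in the placental and cord-blood models, to exposure windows in which preterm birth could be observed.
4. Keep the pooled cohort for other birth outcomes, with birth status at consent and recruitment route as covariates. Repeat these analyses without women enrolled after birth, and within the M@NGO frame alone. Birth status at consent partly reflects gestation at the flood and length of gestation, so show results with and without it.

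A reader might go further and make pre-birth consenters the main set for every birth outcome. That is not recommended. In the simulation only about 20% of women flooded at 25-37 weeks were still pregnant 12 weeks later, and about 4% if consent is spread over 12-20 weeks, so nearly all late exposure would be lost.

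The cost is reduced precision, and no preterm claim for late-pregnancy exposure in the antenatally enrolled set. Delayed entry cannot recover births that could not be observed.
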